### Statistical analysis

The focus of this trial is to compare the efficacy and safety between both study groups. The statistical analyses will be performed on the full analysis set, which will include data from all randomized patients receiving at least one dose of study medication. The safety analysis will include calculation of frequencies, rates of complications, and occurrence of any serious adverse events reported in the two groups.

Descriptive statistics will be calculated according to the scale level of the variables. Continuous data will be analyzed using Student’s *t* test. The chi-square test will be used for categorical variables. A value of *P* < 0.05 will be used to denote statistical significance.

The effect of treatment will be expressed as relative risk estimates and absolute risk reduction. The primary outcome will be analyzed using multivariate logistic regression, adjusting for clinically relevant baseline imbalances. The remaining secondary outcomes will be analyzed using simple 2 × 2 tables and logistic regression. In all analyses, statistical uncertainty will be quantified via 95% confidence intervals. All statistical data will be analyzed using SPSS Version 12.0 (SPCC Inc., Chicago, IL, USA).

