## Background

In patients with acute coronary syndrome (ACS) who undergo percutaneous coronary interventions (PCI), common recommendations for antithrombotic regimens include dual antiplatelet therapy with aspirin and clopidogrel [1,2]. Clopidogrel is a thienopyridine derivative metabolized by cytochrome P450 to an active metabolite that irreversibly inhibits platelet P2Y_12_ receptors [3]. Although the efficacy of clopidogrel has been well established, it exhibits pharmacodynamic variability in diverse conditions which can be due to the loss-of-function *CYP2C19* allele, drug-drug interactions or clinical factors [4]. High on-treatment platelet reactivity (HPR) after clopidogrel administration is associated with adverse cardiovascular events [5-11] and the rate of HPR can be reduced with either a higher loading dose (LD) or maintenance doses (MD) of clopidogrel, or a potent alternative drug [2,12-14]. The use of double doses of clopidogrel and the more potent thienopyridine prasugrel to reduce HPR and subsequent cardiovascular events have not been successful, partially due to the studies being conducted with low event rates and low-risk patients [15,16]. Another issue concerning prior study design has been the delayed administration of drugs, administered after PCI in both cases. Therefore, a platelet reactivity (PR) guided trial with reloading of a more potent drug in the early phase of ACS, especially before PCI, is warranted.

Prasugrel is also a thienopyridine derivative. However, the metabolism of prasugrel is much more efficient than that of clopidogrel, because it occurs via esterases and has less dependency on cytochrome P450 enzymes [17]. As a result, prasugrel treatment results in more rapid onset, more consistent conversion from the inactive prodrug to active metabolite, and higher blood concentrations of the active metabolite [18]. A LD of prasugrel 60 mg results in more rapid, potent and consistent inhibition of platelet function than clopidogrel LDs of 300 mg or 600 mg [19].

We hypothesize that for patients with HPR after an initial LD of clopidogrel, reloading with prasugrel in the early phase of ACS will reduce PR more effectively than reloading with clopidogrel, resulting in a reduction of adverse cardiovascular events.

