### Sample size

The sample size calculation is based on the primary outcome and the primary analysis for the intention-to-treat population. The sample size is calculated using the study’s primary objective to detect a 15% difference in PR suppression between reloading with prasugrel and clopidogrel, to a power of 80% to demonstrate difference. On the basis of previous reports we assume the inhibition of PR after a LD of clopidogrel to be approximately 55% of baseline [22]. The assumed inhibition of PR after LD of prasugrel is 70%. This was calculated from studies showing a 30% higher concentration of the active metabolite in patients of East Asian ethnicity [23] and an approximate 90% inhibition of baseline PRU two hours after a prasugrel 30 mg LD was given in healthy Korean people [24]. We expect the difference in PR inhibition will be at least 15% when considering ACS patients. We adjusted the sample size for an estimated follow-up loss rate of 20%, a two-sided level of significance of α = 5%, which determined that 38 patients in each group would be required to detect this difference with a two-sided Student’s *t* test. A total of 76 patients will be randomized and included in the analysis. We predict that 50% of patients will exhibit HPR as determined by VerifyNow (Accumetrics, San Diego, CA, USA) after receiving the clopidogrel LD. A total of 152 patients will be screened and 76 patients will be randomized and included in the analysis, with 38 patients in each group.

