The GRAVITAS [16] and TRIGGER-PCI [15] trials aimed to detect reductions in HPR and concluded negative results. However, these studies did not use reloading or include high risk, acute phase patients. Our study is therefore the first to involve early manipulation of HPR using a more potent agent before or during PCI. The TRITON-TIMI 38 trial was noted for a lack of clopidogrel loading before randomization. Our trial design addresses some ethical issues arising from such protocols, due to closer similarities with real-world treatment. We anticipate that our study will reveal the possible role of prasugrel reloading and maintenance in improving clinical outcomes, emphasizing its potential to become an integral component in the management of patients undergoing PCI with remaining HPR after a loading dose of clopidogrel.

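### At 38 per arm, the logistic regression and relative risks planned for the rarer 30-day clinical and bleeding outcomes will often give no usable estimate or interval, and the adverse-event hypothesis is severely underpowered

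*Protocol article*

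**What the plan says.** The protocol's Statistical analysis section fixes four things for the secondary outcomes:

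- The test: "The chi-square test will be used for categorical variables", with P below 0.05 as the threshold.
- The model: "The remaining secondary outcomes will be analyzed using simple" two-by-two tables and logistic regression.
- The effect measures: relative risk and absolute risk reduction.
- The precision: "In all analyses, statistical uncertainty will be quantified via 95% confidence intervals".

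Measurement of outcomes lists the 30-day secondary outcomes as cardiovascular death, MI, stent thrombosis, stroke, and bleeding by TIMI and BARC criteria. Table 2 adds target vessel revascularization. HPR at four hours and at 30 days is also secondary.

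The Sample size section sets 38 patients per arm to "detect a 15% difference in PR suppression between reloading with prasugrel and clopidogrel". No clinical event rate enters that calculation.

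The Background hypothesises that better platelet suppression follows from prasugrel reloading, "resulting in a reduction of adverse cardiovascular events". The Discussion extends the superiority hypothesis to adverse events, periprocedural MI among them, and adds: "We anticipate that our study will reveal the possible role of prasugrel reloading and maintenance in improving clinical outcomes". It also names bleeding as a major safety concern. Nothing marks the clinical outcomes as exploratory.

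**The concern.** Logistic regression by maximum likelihood and the relative risk both need events in each arm. If one arm has none, the odds ratio estimate runs to 0 or infinity and its Wald interval is useless. The relative risk is 0 or infinite, with no log-scale interval. If neither arm has events, both measures are undefined. With 38 per arm, this is a likely result for uncommon 30-day events, so the interval promised for every analysis could not be delivered for some outcomes, possibly including the more serious grades of bleeding.

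The second issue is the hypothesis. It reaches to adverse events, but the trial is sized on a laboratory measure. Without an exploratory label, a non-significant comparison of bleeding or ischaemic events could be taken for reassurance that 76 patients cannot give.

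**Working it through.** **Inputs.** From the protocol: 38 per arm, 1:1 allocation, two-sided 5% level, 20% loss (about 30 evaluable per arm). Assumed, because the protocol gives none: event rates of 1% to 20% per outcome, with a halving as the treatment effect.

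**The plan's own figure.** The SD behind 38 per arm is not stated, so the figure can only be solved backwards. With n = 2(1.96 + 0.84)² × SD² / 15², an SD of 20.5 points gives 29.3, rounded up to 30, and 30 / 0.8 = 37.5, rounded up to 38. The size is thus consistent with a comparison of mean platelet inhibition. It carries no information about clinical events.

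**Step 1: empty arms.** With rate p in both arms, P(no events in one given arm) = (1 − p)^38, P(at least one arm empty) = 1 − [1 − (1 − p)^38]², and P(both empty) = (1 − p)^76. For p = 2%: 0.98^38 = 0.464, so 1 − 0.536² = 0.713 and 0.464² = 0.215. If prasugrel halves the rate, one factor uses p/2.

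| Rate p | At least one arm empty, equal rates | Both empty, equal rates | At least one arm empty, prasugrel at p/2 |
|---|---|---|---|
| 1% | 90% | 47% | 94% |
| 2% | 71% | 22% | 83% |
| 3% | 53% | 10% | 70% |
| 5% | 26% | 2% | 47% |
| 10% | 4% | <0.1% | 16% |

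With 30 evaluable per arm, the equal-rate column becomes 93%, 79%, 64%, 38% and 8%.

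**Step 2: chi-square.** The true size of the uncorrected test at a nominal 5% was found by enumerating all pairs of counts at 38 per arm, with 0 versus 0 counted as non-rejection. It is 0.08%, 0.6%, 1.7% and 4.1% at rates of 1%, 2%, 3% and 5%; 5.8% at 10%; 5.3% at 15%; and 5.0% at 20%. Expected counts stay below 5 per arm up to a rate of 5/38 = 13.2%, yet the worst inflation seen is under one percentage point. Single tables can still depend on the test: 4 versus 0 events gives P = 0.040 by chi-square and 0.115 by Fisher.

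**Step 3: power to detect a halving,** by the same enumeration.

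| Control rate | Chi-square | Fisher | Needed per arm for 80% power |
|---|---|---|---|
| 5% | 5.2% | 0.4% | 906 |
| 10% | 13.9% | 3.7% | 435 |
| 20% | 23.6% | 14.9% | 199 |

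The test is symmetric in the arms, so chi-square power to detect a doubling of bleeding from 5% to 10%, or from 10% to 20%, is likewise about 14% or 24%.

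**Step 4: what sparse data can still say.** No events in 38 is compatible with a true rate up to 1 − 0.05^(1/38) = 7.6% (one-sided 95%). A score interval for the risk difference survives even 0 versus 0. For a difference d, the constrained estimates are d and 0, and the Miettinen-Nurminen variance is (76/75) × d(1 − d)/38. Solving gives d = 3.893 / (38 + 3.893), where 3.893 = 1.96² × 76/75. The interval is about −9.3 to +9.3 points.

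**The case against.** The strongest reply has four parts.

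*The chi-square test is not shown to fail.* A reader might infer from small expected counts that it is invalid here. Step 2 does not support that: it is conservative for rare events, close to nominal elsewhere, and undefined only when both arms are empty. Fisher's test would cut already low power further. This part stands.

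*Rarity is assumed.* The protocol gives no event rates. Periprocedural MI or any BARC bleeding may be common enough to avoid empty arms, and HPR at four hours and 30 days is not affected. This stands too, and limits the point to the rarer outcomes.

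*The protocol does not overclaim.* A reader might infer that it asserts the trial will show fewer events, or that it claims power for them. It does neither. The Background and Discussion hypothesise and anticipate, Trial objectives confines the primary aim to platelet reactivity, and the clinical events are classed as secondary. Still, the Discussion states superiority for adverse events as part of the hypothesis, without an exploratory label.

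*Sparse-data fallbacks belong in an analysis plan, and part of the plan survives.* The absolute risk reduction remains computable with one empty arm, and the safety analysis already includes frequencies and rates. Both are true. But the article is not silent on method: it names logistic regression for these outcomes and promises intervals in every analysis. An analysis plan would have to depart from that text, not merely fill it in.

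**Conclusion.** The point holds for the rarer 30-day clinical and bleeding outcomes. At assumed equal rates of 1% to 5%, between 90% and 26% of trials of this size leave at least one arm without events, and the named logistic model and relative risk then give no usable estimate or interval. At 10% the problem is uncommon (4%, or 16% if prasugrel halves the rate).

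It would go too far to call the adverse-event hypothesis untestable. A test can be run, but its power to detect a halving is at most about 24% for control rates up to 20%, so the hypothesis is severely underpowered. The primary analysis is not touched. The weight is moderate: these are secondary outcomes, but they include a named safety concern and part of a stated hypothesis. All probabilities rest on the assumed rates and on 38 analysed per arm; with 30, they are worse.

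**What to change.** In Statistical analysis, report each 30-day clinical and bleeding outcome as counts per arm and a risk difference with a Miettinen-Nurminen or exact 95% confidence interval. For these outcomes, drop logistic regression or use Firth penalisation when events are sparse. Label them exploratory. In the Background and Discussion, limit the confirmatory hypothesis to platelet reactivity. Replacing chi-square with Fisher's exact test is optional, because it lowers power further.

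No extra patients or data are needed. The costs are rewording, more modest clinical claims, and possibly software other than the named SPSS 12.0, whose support for these intervals and for penalised regression has not been checked here.

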### Randomization

Random treatment assignments will be generated using Excel spreadsheet software (Microsoft Corporation, Redmont, DC, USA). Eligible patients will be randomly assigned, on a 1:1 ratio, to receive reloading with either prasugrel or clopidogrel. Treatment randomization will be performed by independent personnel not involved in the study.

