### Intervention and comparator descriptions

Before randomization, 300 mg of aspirin and 600 mg of clopidogrel will be administered as LDs according to the conventional guidelines for ACS [2]. For those who have already been receiving clopidogrel for five days or more, 300 mg of clopidogrel will be administered as a LD. PR will be evaluated before PCI and defined as the time between the arrival of the patient at the angiography room, and the beginning of coronary angiography. Angiography will not begin before confirmation of PRU. Patients who exhibit HPR defined as a PRU value of 240 units or more by VerifyNow (Accumetrics, San Diego, CA, USA) will be randomized and followed by assignment to either the clopidogrel reloading group (clopidogrel 300 mg) or the prasugrel reloading group (prasugrel 20 mg). Angiography in patients with HPR will begin after administration of the study drug. PR will be checked serially using the VerifyNow (Accumetrics, San Diego, CA, USA) assay at four hours, 24 hours and 30 days after PCI. Patients will be required to visit the outpatient clinic at Day 30 for measurement of PR. For patients discharged before Day 8, a secondary visit at Day 15 will be recommended.

In the clopidogrel reloading group, 300 mg clopidogrel will be reloaded, followed by MDs of clopidogrel 75 mg/day for 30 days. In the prasugrel reloading group, 20 mg of prasugrel will be reloaded, followed by prasugrel administration of 5 mg/day for 30 days.

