### Measurement of outcomes

The primary endpoint of this study will be HPR at 24 hours after PCI, as determined by the VerifyNow (Accumetrics, San Diego, CA, USA) assay during the study period (Table 2). The optimal cutoff value is defined as 240 units, as observed by Marcucci *et al*. [9]. Secondary endpoints include major adverse cardiovascular events at 30 days after PCI, including death from cardiovascular cause, myocardial infarction (MI), stent thrombosis, hemorrhagic or non-hemorrhagic stroke, and bleeding events defined by Thrombolysis in Myocardial Infarction (TIMI), as well as Bleeding Academic Research Consortium (BARC) criteria. HPR at four hours or 30 days after PCI will also be evaluated.

**Table 2 T2:** Primary and secondary outcomes

**Primary outcome**	**Secondary outcomes**
HPR (PR ≥ 240 units)	Death from cardiovascular cause
	Myocardial infarction
	Stent thrombosis
	Hemorrhagic or non-hemorrhagic stroke
	Target vessel revascularization
	Bleeding event defined by Thrombolysis in Myocardial Infarction (TIMI) criteria and BARC

HPR, high platelet reactivity: more than 240 units determined via VerifyNow (Accumetrics, San Diego, CA, USA); PR, platelet reactivity; BARC, bleeding academic research consortium.

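### The primary logistic model takes its covariates from observed baseline imbalances; pre-randomisation PRU should be fixed as the covariate in advance

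*Protocol article*

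**What the plan says.** Under Measurement of outcomes, "The primary endpoint of this study will be HPR at 24 hours after PCI", a binary outcome with a 240-unit cutoff. Statistical analysis gives its model: "The primary outcome will be analyzed using multivariate logistic regression, adjusting for clinically relevant baseline imbalances". That section lists no covariates, sets no threshold for imbalance and puts no limit on how many variables may enter.

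Intervention and comparator descriptions shows that the baseline value of the endpoint variable is known for everyone randomised, because it decides entry: "Patients who exhibit HPR defined as a PRU value of 240 units or more by VerifyNow" are the ones randomised. The same section describes two initial loads. The usual one is "300 mg of aspirin and 600 mg of clopidogrel will be administered as LDs", and there is an exception: "For those who have already been receiving clopidogrel for five days or more, 300 mg of clopidogrel will be administered as a LD". Randomization says "Eligible patients will be randomly assigned, on a 1:1 ratio" and mentions no stratification factor.

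**The concern.** Randomisation makes any baseline imbalance a chance event. A variable can differ between arms and say nothing about 24-hour HPR, or be well balanced and predict it strongly. Adjustment helps through prediction, so selecting on imbalance uses the wrong criterion.

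Two things follow. First, the confirmatory model cannot be written down before the baseline comparison is seen, and two careful analysts could defend different models. Second, pre-randomisation PRU, the obvious candidate predictor, enters only if it happens to differ between arms. What is at stake is some power in a small trial, and a primary result that can be traced to a model fixed beforehand.

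This is more than a detail left to an analysis plan. The protocol states a data-dependent rule, and a later plan with fixed covariates would have to replace it.

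**Working it through.** **Evaluable patients.** The protocol gives no power for the logistic model. Its only size figure is 38 per group, from a t test on a 15-point difference in mean inhibition with 20% loss. The SD is not stated, so 38 cannot be checked directly. With n = 2(1.960 + 0.842)² SD²/15², an SD of 20.7 gives 2 × 7.85 × 428.5/225 = 29.9, so 30, and 30/0.8 = 37.5, so 38. I therefore take 30 evaluable per arm.

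**How often the rule admits baseline PRU.** If imbalance means p<0.10 (an assumption, since the protocol gives no criterion), randomisation alone fixes the chance at about 10%. The simulated frequencies were 8.9 to 11.3%.

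**Simulation set-up.** 1,500 trials per scenario. Baseline B is half-normal above 240, because the Sample size section predicts 50% HPR after loading, which puts the median near 240. B is then standardised. The latent 24-hour value is L = ρB + √(1 − ρ²)E, with HPR when L exceeds the cutoff that gives the arm's assumed rate. The treatment test is the likelihood-ratio statistic 2(l₁ − l₀) on 1 degree of freedom. The protocol gives neither ρ nor the 24-hour HPR rates, so both are assumed and varied.

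**Power (%):**

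| HPR, clopidogrel vs prasugrel | ρ | Unadjusted | PRU only if imbalanced (p<0.10) | PRU fixed | Gain, fixed minus triggered |
|---|---|---|---|---|---|
| 50 vs 20 | 0 | 69.9 | 69.6 | 69.1 | −0.5 |
| 50 vs 20 | 0.3 | 70.7 | 71.2 | 73.5 | 2.3 |
| 50 vs 20 | 0.5 | 71.6 | 72.5 | 78.3 | 5.8 |
| 40 vs 15 | 0 | 62.0 | 61.4 | 60.7 | −0.7 |
| 40 vs 15 | 0.3 | 64.7 | 64.5 | 65.7 | 1.2 |
| 40 vs 15 | 0.5 | 62.5 | 62.9 | 69.3 | 6.4 |

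A separate simulation at 50% vs 20% gave 70, 70 and 68% for imbalance-triggered adjustment and 71, 74 and 77% for fixed PRU at ρ = 0, 0.3 and 0.5, which are gains of 1, 4 and 9 points. Together these support roughly 0 to 9 points. At ρ = 0.7 the first simulation gains 88.1 − 75.6 = 12.5 and 79.3 − 64.6 = 14.7 points. I give that correlation less weight because entry at 240 or above truncates the baseline range.

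**Type I error (50% in both arms, ρ = 0, 0.3, 0.5):**

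| Analysis | Rejection (%) |
|---|---|
| Unadjusted | 5.5, 5.4, 5.4 |
| PRU only if imbalanced | 5.5, 5.0, 4.9 |
| PRU fixed | 5.9, 5.5, 5.9 |
| Lowest p among models using covariates with imbalance p<0.20 | 7.6, 7.4, 7.9 |
| Lowest p among unadjusted, PRU, and PRU plus one of 8 noise covariates | 8.3, 9.0, 10.3 |

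At ρ = 0.7 the last two rows are 8.7 and 10.9. The Monte Carlo standard error near 5% is √(0.05 × 0.95/1500) = 0.56 points. The fixed-PRU test rejects 0.4 to 1.0 points more often than the triggered one under the null, so a small part of the power gain may reflect the likelihood-ratio test in small samples.

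A further check entered every covariate found imbalanced at p<0.2 or p<0.05 (baseline PRU plus 9 noise covariates, 4,000 replicates). Type I error was 5.2 to 5.6% by likelihood ratio and 4.6 to 5.0% by Wald test, against 5.4 to 5.6% unadjusted.

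**The case against.** A reader might infer that the rule inflates the false-positive rate. The documents do not support that. The 7 to 11% figures come from fitting several models and keeping the smallest treatment p-value, which the protocol does not propose. Adjusting for whatever is imbalanced, as written, holds close to 5%. The Discussion also says that those who record and analyse the data do not know the allocation. This makes choosing a model by its result less likely, although treatment is open-label. It does not make the model known in advance.

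The power gain rests on a correlation that the protocol does not give, and truncation at 240 may weaken it. That stands, and it is why the gain is given as a range starting at zero.

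A reader might also want initial loading regimen fixed as a covariate, or randomisation stratified by it. Nothing in the protocol says how many patients will already be on clopidogrel or that they respond differently. With about 60 evaluable patients, a small subgroup forced into a logistic model risks sparse cells. An article's silence on stratification is not a fault.

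Larger gains can be shown for covariance analysis of continuous PRU, but the primary endpoint is binary.

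Finally, covariate lists often sit in an analysis plan, and one may exist. That excuses a missing list, not a stated imbalance trigger.

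**Conclusion.** The point holds in a limited form. The protocol ties the primary model to chance imbalances, leaves it undetermined until data are seen, and would usually omit the one baseline measurement made on the endpoint's own scale. The expected loss is a few points of power: roughly 0 to 9 with 30 evaluable per arm, assumed correlations of 0 to 0.5, and assumed 24-hour HPR of 50% vs 20% or 40% vs 15%. If baseline PRU is not prognostic, fixing it costs under one point relative to the triggered rule. Type I error under the rule as written is not a reason for the change. A fixed model does, however, close off the worst case of choosing by p-value. This is a should-fix.

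**What to change.** Replace the covariate clause with wording such as: The primary analysis of 24-hour HPR is a logistic regression on treatment group and pre-randomisation PRU (continuous), fixed in advance. Any adjustment prompted by observed baseline imbalance, including for initial clopidogrel loading regimen, is a sensitivity analysis only.

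The section also promises "The effect of treatment will be expressed as relative risk estimates and absolute risk reduction"; these should be obtained from the same fixed model.

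The cost is one sentence, agreed before outcomes are compared between groups. PRU is already measured in every randomised patient, and no visit, treatment or sample size changes. One covariate is also a modest demand on about 60 evaluable patients.
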